12. Weekly dosing: Decision to return to weekly dosing PRO051 will be made after full discussion between principal investigator and medical monitor

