## **3.3      Study evaluations**

Appendix 2 depicts the schedules of assessments throughout the study. Table 4 shows the assessments to be done during the study period (visit 1 – 12). Table 5 specifies the assessments to be done during each hospitalization visit (visit 2 – 6). In Tables 6 - 14 is depicted the schedule of assessments to be done during the treatment beyond study.

Total blood volume during the study period to assess effect, safety laboratory and pharmacokinetic parameters is maximally 200 ml for each study participant, divided over 13 visits during a 18-week (4 ½ months) period. Main burden will be during the 5-week treatment period.

In the treatment beyond study period, the total blood volume to assess effect, safety laboratory and pharmacokinetic parameters is for each study participant as follows.

- maximally 140 ml during the period of the 1st week visit u/l the 13th week visit. Main burden will be at week 1, 5, 9, and 13.
- maximally 125 ml during the period of the 14th week visit u/l the 25th week visit. Main burden will be at week 17, 21, and 25.
- maximally 135 ml during the period of the 26th week visit u/l the 49th week visit. Main burden will be at week 29, 33, 37, 41, 45, and 49.
- maximally 122 ml during the period of the 50th week visit u/l the 73rd week visit. Main burden will be at week 53, 57, 61, 65, 69, and 73.
- maximally 157 ml during the period of the 74th week visit u/l the 97th week visit. Main burden will be at week 77, 81, 85, 89, 93, and 97.
- maximally 157 ml during the period of the 98th week visit u/l the 121nd week visit. Main burden will be at week 101, 106, 109, 113, 118 and 121.
- maximally 157 ml during the period of the 122nd week visit u/l the 145th week visit. Main burden will be at week 125, 130, 133, 137, 142, and 145.
- maximally 157 ml during the period of the 146th week visit u/l the 169th week visit. Main burden will be at week 148, 154, 157, 161, 166 and 169.
- maximally 157 ml during the period of the 170th week visit u/l the 193rd week visit. Main burden will be at week 172, 177, 180, 184, 189 and 192.
- maximally 157 ml during the period of the 194th week visit u/l the 217th week visit. Main burden will be at week 196, 201, 204, 208, 213 and 216.

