### **5.6.5 Safety laboratory**

### **5.6.5.1      Routine biochemistry and hematology**

Routine biochemistry and hematology will be performed at selected visits, refer to Tables 6 - 14 in Appendix 2 for the exact time points.

The parameters to be assessed for routine biochemistry and hematology are described in Appendix 3. There is no food restriction prior to blood sampling. The samples will be collected and processed according to standard hospital procedures and assessed by the local laboratory of the participating sites.

Non-clinical studies with PRO051 suggest that it potentially may have hepatotoxic and nephrotoxic properties as it accumulates in the liver and kidney and is also associated with thrombocytopenia.

Therefore, monitoring of hepatic and renal function as well as thrombocyte count is of paramount importance. However, standard markers of hepatic and renal function may be confounded by the effects of DMD e.g. DMD subjects may have elevated ALAT, ASAT and CK levels (common markers of hepatic function) due to 'leaky' sarcolemmal membranes around muscle fibers, and serum and urinary creatinine concentrations (markers of renal function) may be variable due to changes in muscle mass. With this information in mind, the following parameters will be used for monitoring hepatic and renal function:

Hepatic function:      ALAT, ASAT, ALP, total bilirubin, bilirubin fractions (direct bilirubin),  $\gamma$ -GT, GLDH and LDH.

Renal function:      Urinalysis (including microscopy), serum and urine cystatin C, KIM-1, alpha-1-microglobulin and serum creatinine.

Urinalysis will be conducted on the first morning specimen after 8 hours of not drinking.

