6. Parameters will be derived from M-mode measurements and include left ventricular ejection fraction, fractional shortening, left ventricular posterior wall thickness, left ventricular septum wall thickness, left ventricular end systolic diameter, left ventricular end diastolic diameter, and left ventricular ejection fraction modified Simpson's
7. Via finger prick
8. Prior to study medication administration and at  $t = 0.5 \text{ hr} (\pm 5 \text{ min})$ ,  $2 \text{ hr} (\pm 15 \text{ min})$ ,  $3 \text{ hr} (\pm 15 \text{ min})$ ,  $4 \text{ hr} (\pm 15 \text{ min})$ ,  $6 \text{ hr} (\pm 15 \text{ min})$ ,  $9 \text{ hr} (\pm 30 \text{ min})$ ,  $12 \text{ hr} (\pm 30 \text{ min})$  and  $24 \text{ hr} (\pm 3 \text{ hrs})$  after study medication administration
9. Window is  $\pm 3$  days
10. Timed tests consist of: 10-meter walk/run, rising from floor, stair climb
11. Parameters include FVC, FEV1, mouth pressure inhale, mouth pressure exhale, peak flow, peak cough flow
12. The investigator or study coordinator will contact subject/parent at four days after study medication administration ( $t = 96 \pm 9 \text{ hrs}$ ) to enquiry about the health of the subject and to assess the adverse events and concomitant medication. In case patient and/or parent do not respond to e-mail/SMS, a phone call is still needed

Table 7. Schedule of assessments for visits 38 – 61 (treatment beyond study period)

| Visit                                        | 38                     | 39    | 40    | 41    | 42    | 43    | 44    | 45    | 46    | 47    | 48    | 49    | 50    | 51    | 52    | 53    | 54    | 55    | 56    | 57    | 58    | 59    | 60    | 61    | Withdrawal |
|----------------------------------------------|------------------------|-------|-------|-------|-------|-------|-------|-------|-------|-------|-------|-------|-------|-------|-------|-------|-------|-------|-------|-------|-------|-------|-------|-------|------------|
| Day (window ± 1 day)                         | d+175                  | d+182 | d+189 | d+196 | d+203 | d+210 | d+217 | d+224 | d+231 | d+238 | d+245 | d+252 | d+259 | d+266 | d+273 | d+280 | d+287 | d+294 | d+301 | d+308 | d+315 | d+322 | d+329 | d+336 |            |

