| Urine protein/creatinine                     |                        | x     |       | x     |       | x     |       | x     |       | x     |       | x     |       |       |       | x     |       |       |       |       |       |       |       | x     | x          |
| Urine α-1-microglobulin                      |                        |       |       |       |       |       |       |       |       |       |       | x     |       |       |       |       |       |       |       |       |       |       |       | x     | x          |
| Safety biochemistry                          |                        |       |       | x     |       |       |       | x     |       |       |       | x     |       |       |       | x     |       |       |       |       |       |       |       | x     | x          |
| Safety haematology                           |                        |       |       | x     |       |       |       | x     |       |       |       | x     |       |       |       | x     |       |       |       |       |       |       |       | x     | x          |
| Thrombocyte count                |                        | x     |       |       |       | x     |       |       |       | x     |       |       |       | x     |       |       |       | x     |       | x     |       | x     |       | x     |            |
| Complement (C3)                              |                        |       |       | x     |       |       |       | x     |       |       |       | x     |       |       |       | x     |       |       |       | x     |       |       |       | x     | x          |
| Troponin                                     |                        |       |       | x     |       |       |       | x     |       |       |       | x     |       |       |       | x     |       |       |       | x     |       |       |       | x     | x          |
| Fibrinogen                                   |                        |       |       | x     |       |       |       | x     |       |       |       | x     |       |       |       | x     |       |       |       | x     |       |       |       | x     | x          |
| Haptoglobin                                  |                        |       |       | x     |       |       |       | x     |       |       |       | x     |       |       |       | x     |       |       |       | x     |       |       |       | x     | x          |

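### Table 7 schedules no liver, kidney or urine protein tests at Visit 57, leaving an unexplained 56-day interval under weekly dosing that does not fit the priority given to this monitoring in section 5.6.5.1

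*Protocol*

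**What the plan says.** Appendix 2, Table 7 covers Visits 38 to 61 of the treatment beyond the study period. Study drug is marked at every one of these visits, and footnote 1 places the other assessments before the dose unless stated otherwise.

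- "Safety biochemistry" and "Safety haematology" are marked at Visits 41, 45, 49, 53 and 61.
- The general urine row and "Urine protein/creatinine" are marked at Visits 39, 41, 43, 45, 47, 49, 53 and 61.
- "Urine α-1-microglobulin" and serum cystatin C are marked at Visits 49 and 61 only.
- C3, troponin, fibrinogen, haptoglobin, CRP, aPTT and ECG are marked at Visits 41, 45, 49, 53, 57 and 61.
- Finger-prick thrombocyte counts are marked at Visits 39, 43, 47, 51, 55, 57, 59 and 61.

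Section 3.3, on blood volume for the 26th to 49th week visits, says: "Main burden will be at week 29, 33, 37, 41, 45, and 49".

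Section 5.6.5.1 states that "monitoring of hepatic and renal function as well as thrombocyte count is of paramount importance", and leaves the time points of biochemistry and haematology to Tables 6 to 14. Section 5.6.8.1 sets hepatic criteria, each of which needs ALAT or γ-GT. Section 5.6.5.9 sets urine criteria, several of which need two samples in a row.

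**The concern.** Because section 5.6.5.1 leaves the timing to the tables, a blank cell means that no test is scheduled. At Visit 57 the liver, kidney and urine protein rows are blank while blood is drawn for six other tests, and no footnote explains it.

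Three things are at stake. First, the ALAT and γ-GT criteria in 5.6.8.1 and the urine protein criteria in 5.6.5.9 have no scheduled input between Visits 53 and 61. Second, for the urine criteria that need two samples in a row, the sample following Visit 53 comes eight weeks later. Third, section 8.5.1 summarises quantitative parameters by visit, and section 8.5.5.4 adds shift tables. At Visit 57 these will show CRP and C3 with no scheduled liver enzymes, creatinine or CK beside them. A reader of the extension safety tables could take the lack of abnormal liver or kidney results in this stretch as reassurance, when no test was scheduled.

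**Working it through.** No sample-size or error-rate figure is involved; this is a check of the schedule.

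**1. Match weeks to visits.** Visit 13 is the first week visit of the extension, so the Nth week visit is Visit N + 12. The section 3.3 weeks for this block become:

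| Week in 3.3 | 29 | 33 | 37 | 41 | 45 | 49 |
|---|---|---|---|---|---|---|
| Visit | 41 | 45 | 49 | 53 | 57 | 61 |
| C3, CRP, aPTT marked | yes | yes | yes | yes | yes | yes |
| Biochemistry and haematology marked | yes | yes | yes | yes | **no** | yes |
| Urine protein/creatinine marked | yes | yes | yes | yes | **no** | yes |

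**2. Length of the gap.** Visit 53 is d+280 and Visit 61 is d+336: 336 − 280 = 56 days. Tests precede the dose, so the doses between the two panels are those of Visits 53 to 60: 60 − 53 + 1 = 8. On the 4-weekly spacing the figures are 28 days and 4 doses. An abnormality that begins just after the Visit 53 sample could thus wait up to 56 days for a scheduled test, against 28.

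**3. Compare with the rest of the schedule.** Biochemistry is marked at Visits 13, 17, 21, 25, 29, 33 and 37 (Table 6), at 41, 45, 49, 53 and 61 (Table 7), and at 65, 69, 73, 77, 81 and 85 (Table 8). Up to Visit 85 every interval is 4 weeks except 53 to 61. In Tables 9 to 14 the intervals are 3, 4 or 5 weeks. The 8-week interval is therefore the longest in Tables 6 to 14, and it falls under continuous weekly dosing.

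**4. Compare with section 3.3 up to week 73.** That section lists 4 + 3 + 6 + 6 = 19 main weeks up to week 73. Eighteen coincide with a biochemistry and haematology panel; week 45 alone does not.

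**5. Could other rows fill the gap?** Urine α-1-microglobulin and serum cystatin C are marked at 49 and 61, so they do not. The two-weekly urinalysis in 5.6.8.2 belongs to the 12-week cycles that begin after Visit 85, so it does not apply here. Platelets are different: finger-prick and haematology visits together give 39, 41, 43, 45, 47, 49, 51, 53, 55, 57, 59 and 61, an unbroken two-weekly series.

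**The case against.** The strongest reply is that this is a planned reduction. Urine testing thins in steps: weekly to Visit 29, two-weekly to Visit 49, then Visit 53, then Visit 61. Four rows stop in the same column, and a finger-prick count appears at Visit 57, just where full haematology is absent. That looks more like design than a dropped mark. The possibility stands. Against it, no reason is given, biochemistry returns to 4-weekly at Visit 65 after this single interval, and a finger-prick count is also marked at Visit 61, where haematology is done anyway. Platelet counts do not replace liver or kidney tests.

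A reader might infer that section 3.3 and Table 7 contradict each other outright. They do not: section 3.3 speaks of blood volume and names no tests, and Table 7 does draw blood at Visit 57.

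A reader might also infer that one of six intended panels is missing, or that the stopping criteria cannot be applied in this interval. No passage says that six panels were intended. Nothing forbids unscheduled tests, and adverse events are recorded at every visit, so the criteria lack scheduled input rather than being unusable. The INR arms of the hepatic criteria have no scheduled test anywhere in Table 7, so Visit 57 is not what leaves those arms empty.

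Finally, Visit 57 has very likely passed. Section 5.6.5.5 refers in the past tense to a measurement at Visit 85, 28 weeks later, and the schedule now runs to Visit 229. Table 7 may be an older schedule kept beside newer safety text. That limits what can still be changed, but not what should be explained and reported.

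**Conclusion.** The point holds as an unexplained break in the 4-weekly pattern. Its size is one interval of 56 days and 8 doses without a scheduled liver, kidney or urine protein test, for every boy treated on Table 7. It conflicts with the priority stated in section 5.6.5.1 and leaves the ALAT and γ-GT criteria in 5.6.8.1 and the urine protein criteria in 5.6.5.9 without scheduled input. It does not extend to platelets, and whether the omission was intended cannot be settled from the protocol.

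The conclusion assumes that the printed table is as the sponsor meant it to appear. A lost mark is unlikely, since four rows are blank in the same column while other rows are marked there.

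**What to change.** Reconcile the Visit 57 column of Table 7 with sections 3.3, 5.6.5.1, 5.6.5.9 and 5.6.8.1, and state whether the omission of biochemistry, haematology and urine is intended. If it is, give the reason in a footnote. Which schedule is right is for the sponsor to decide.

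For boys who have already passed Visit 57, the report on the treatment beyond the study period (section 8.6) should state that no liver or kidney tests were scheduled for the eight weeks from Visit 53 to Visit 61. It should list any unscheduled results from that interval, with the number of boys tested, so that an empty Visit 57 is not counted as a normal one.

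The cost is a few table cells or one footnote in an amendment, and a sentence and a short listing in the report. Blood is already scheduled to be drawn at this visit, so no extra visit is involved whichever way the passages are reconciled.

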## Appendix 3 Parameters for routine hematology, biochemistry and urinalysis assessment

### Hematology parameters

Hemoglobin  
MCV  
Erythrocyte count  
Hematocrit  
MCH (hemoglobin/erythrocyte count)  
MCHC (hemoglobin/hematocrit)  
Leukocyte count  
Leukocyte differential count:  
– Basophils  
– Eosinophils  
– Lymphocytes  
– Monocytes  
– Neutrophils  
Reticulocyte count  
Thrombocyte count  
Blood smear for schistocytes

### Coagulation parameters (blood)

Activated partial thromboplastin time (aPTT)  
PTT (INR)

### Biochemistry parameters (blood)

Sodium  
Potassium  
Calcium  
Urea  
Creatinine  
Aspartate aminotransferase (ASAT)  
Alanine aminotransferase (ALAT)  
Gamma glutamyl transferase ( $\gamma$ -GT)  
Lactate dehydrogenase (LDH)  
Alkaline phosphatase (ALP)  
Creatinine kinase (CK)  
Glutamate dehydrogenase (GLDH)  
Bilirubin  
Amylases  
Total protein  
Albumin  
Albumin/globulin ratio  
Glucose  
Cholesterol  
  
MCP-1 (Monocyte chemotactic protein-1)  
Cystatin-C

### Urinalysis a

Glucose  
Albumin  
Protein  
Creatinine  
  
Every 4 weeks include;  
 $\alpha$ 1-microglobulin  
Cystatin C  
Kidney injury molecule-1 (KIM-1)  
  
Protein/creatinine ratio  
  
Microscopy of urine sediment for erythrocytes, leukocytes and casts

a: All parameters are to be measured in the first morning specimen after 8 hours of not drinking

## Appendix 4 Analytical Methods

### I. Patient Screening

#### Skin biopsy – *in vitro* dystrophin mRNA

Skin biopsies taken from the patients during the screening period will be stored and transported in cell proliferation culture medium at ambient temperature. Fibroblasts will be isolated, preferably within 48 hours after sampling, by enzymatic dissociation of the skin tissue. After a series of proliferation cycles, approximately  $2 \times 10^6$  fibroblasts per ampoule will be stored in culture freezing medium under liquid nitrogen as backup. For the screening assay, proliferating fibroblasts will be plated in a 6-wells dish and converted into differentiating muscle-like cells by infection with an adenoviral vector expressing the MyoD gene (Ad5fib50 MyoD). These MyoD-converted fibroblasts, now expressing dystrophin, will be transfected with 0, 100 and 250 nM PRO051, in duplo, per dish. A duplo 6-wells dish will be similarly processed using cells from a subsequent cell passage. RNA will be isolated from each well, 24 to 48 hours after transfection, stored at -80 °C, or directly analyzed by RT-PCR analysis using DMD-gene specific primers flanking the patients' mutations. The set of primers may thus differ per patient. All RT-PCR assessments will accordingly be performed in duplo. The duplo dish will be used for back up. Sequence analysis will be performed on isolated PCR products (in duplo per product) to confirm both the mutation and the exon 51 skipping (if occurring) on RNA level.

#### Peripheral blood mononuclear cells (PB-MNC) – *in vitro* dystrophin mRNA (exploratory)

Blood samples taken from the patients collected in EDTA tubes (ambient) will be layered on top of a HistoPaque gradient within 48 hrs after sampling. Upon centrifugation, four layers become visible. The second layer (from top to bottom) contains the mononuclear cells that will be collected, washed, and centrifuged again. The cell pellet will be resuspended in proliferation culturing medium, counted, and either frozen in culture freezing medium or directly processed for further analysis. For this analysis,  $2-8 \times 10^6$  cells per well will be plated in 6-wells plates and cultured for 3 hrs. The cells will be transfected with 0, 100 and/or 250 nM PRO051 (depending on the total amount of cells isolated), in duplo, per dish. RNA will be isolated 72 hrs after transfection, stored at -80 °C, or directly analyzed by RT-PCR analysis using DMD-gene specific primers flanking the patients' mutations. The set of primers may thus differ per patient. All RT-PCR assessments will be performed in duplo. Due to the limited amount of cells that can be isolated from a blood sample another duplo dish will not be included. Sequence analysis will be performed on isolated PCR products (in duplo per product) to confirm both the mutation and the exon 51 skipping (if occurring) on RNA level.

**Note:** The assay's applicability and reproducibility for the indicated purposes is under consideration. Based on the results in this study the assay may replace the original method based on MyoD-conversion of patient-derived fibroblasts.

### II. Study Sample Screening

#### mRNA production in muscle tissue

Muscle biopsies will be taken from the DMD patient at different study time points, to be stored at -80 °C, and sectioned using a pre-cooled cryotome (approximately -25 °C). Total muscle RNA will be isolated from a series of sections of 50 µm up to a total weight of 10 to 15 mg of muscle tissue, and analyzed by semi-quantitative RT-PCR (as recently described). Two different screening procedures will be performed:

1. RT-PCR analysis focusing on the area flanking the targeted exon 51 will be performed to detect specific exon 51 skipping in muscle. Depending on the patient's mutation different sets of DMD-gene specific RT and PCR primers will be used. The

relative skipping efficiencies will be assessed through semi-quantitative LabChip analysis of the PCR products. Sequence analysis will be performed on isolated PCR products to confirm specific exon 51 skipping. All assessments will be performed in triplo.

2. To ensure the sequence-specificity of PRO051, the splicing throughout the entire DMD transcript will be screened for each patient. Total muscle RNA (from one time point only) will be analyzed by RT-PCR with a series of primer sets spanning the DMD gene as described for, or modified from, the Protein Truncation Test.

## **Dystrophin expression in muscle tissue**

The patient muscle biopsies (stored at -80 °C) will be sectioned using a pre-cooled cryotome (approximately -25 °C). Dystrophin expression will be assessed by 1) immunofluorescence analyses of cross-sections and by 2) western blot analyses of total protein extracts, similar to the procedures recently described in van Deutekom et al., 2007).

1. 8 µm cross-sections will be collected on glass slides (two per slide, 10 slides) for immunofluorescence analysis and detection of novel dystrophin expression at the myofiber membranes. The glass slides and remainder of biopsy (embedded in Tissue-Tek) will be stored at -80 °C. The cross-sections will be acetone-fixed and hybridized to a series of primary antibodies, either raised against human dystrophin (MANDYS106 and NCL-DYS2), or against human control muscle proteins such as laminin-alpha2. After hybridization to specific alexa fluor secondary antibodies, an integrated Leica microscope, digital camera and software (LAS) system will be used for signal detection and semi-quantitative measurement of signal intensities. All assessments will be performed in triplo.
2. total muscle protein extracts will be isolated from a series of sections of 50 µm up to a total weight of 20-30 mg of muscle tissue, and analyzed by Western blot analysis to detect and confirm novel dystrophin expression. Different amounts of protein (10 to 100 µg) will be applied per patient. The western blots will be hybridized to primary antibodies against human dystrophin (NCL-DYS1 or MANDYS106) and a human control muscle protein such as dysferlin. An IRDye 800CW secondary antibody will be applied appropriate for signal detection by the Odyssey Infrared Imaging System. Signal intensities will be measured using supplementary Odyssey software. All assessments will be performed in triplo.

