| Name of sponsor                                                                                                                | Prosensa Therapeutics B.V.                                                                                                                                                                                                                                                                                                                                                                                                                      |                                           |
| Name of finished product                                                                                                       | PRO051                                                                                                                                                                                                                                                                                                                                                                                                                                          |                                           |
| Name of active ingredient                                                                                                      | 2'-O-methyl-phosphorothioate antisense oligoribonucleotide named h51AON23                                                                                                                                                                                                                                                                                                                                                                       |                                           |
| Title of study                                                                                                                 | A phase I/II, open label, escalating dose, pilot study to assess the effect, safety, tolerability and pharmacokinetics of multiple subcutaneous doses of PRO051 in patients with Duchenne muscular dystrophy                                                                                                                                                                                                                                    |                                           |

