| Schedule of assessments                                        | See Appendix 2                                                                                                                                                                                                                                                                                                                                                                                                                                                                                                                                                                                                                                                                                                                                                         |

N.B. GlaxoSmithKline will take sponsorship for the study on 21 July 2011 and will supply study drug from that date onwards. For simplicity, the protocol will continue to refer to the drug as PRO051 (PRO051 = GSK2402968).

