### **3.2.4      Method of assigning subjects to treatment groups**

This is an open study in which all study subjects will receive active treatment. Patients will be assigned to a dose level based on the sequence of entering the study.

For safety reasons, there will be an interval of at least 2 days between the start of treatment of each patient within one group.

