### **3.2.5      Blinding**

Not applicable.

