#### **5.2.1.1      mRNA production**

Endogenous production of the expected mRNA will be assessed at the Prosensa laboratory in muscle tissue collected via the muscle biopsy.

For analytical methods refer to Appendix 4.

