#### **5.2.1.2      Dystrophin expression**

Dystrophin expression will be assessed at the Prosensa laboratory in the muscle biopsies by immunofluorescence analyses of cross-sections and by western blot analyses of total protein extracts.

For analytical methods refer to Appendix 4.

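### Dosing is open, but the protocol also leaves the laboratory reader unmasked to cohort and visit for dystrophin and exon-skip read-outs; coding the samples would reduce expectation bias at little cost

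*Protocol*

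**What the plan says.** Section 3.2.4 of the protocol states: "This is an open study in which all study subjects will receive active treatment". Patients are assigned to a dose level by the order in which they enter. Section 3.2.5, Blinding, reads "Not applicable".

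The muscle read-outs are made in one laboratory. Section 5.2.1.1: "Endogenous production of the expected mRNA will be assessed at the Prosensa laboratory". Section 5.2.1.2: "Dystrophin expression will be assessed at the Prosensa laboratory in the muscle biopsies". Section 5.5.1 names the same laboratory for the biopsies taken during treatment beyond the study period. The synopsis names the sponsor as "Prosensa Therapeutics B.V" and adds that "GlaxoSmithKline will take sponsorship for the study on 21 July 2011".

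Appendix 4, part II, gives the methods. For immunofluorescence, a "software (LAS) system will be used for signal detection and semi-quantitative measurement of signal intensities". Exon-skip efficiency comes from a LabChip analysis that is also called semi-quantitative. Western blot intensity is measured by the imaging software. All three are done in triplicate.

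Section 5.2.1 sets the biopsy times: screening and day 43 in cohort 1, day 43 and day 78 in cohorts 2 to 4. Section 3.1 says there is no control group. Section 8.5.5.5 plans no formal analysis of dystrophin presence and localization.

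**The concern.** An open-label design settles who knows the dose at the bedside. It does not settle who knows it at the microscope, the blot or the PCR read-out, and those readings can be masked whatever the dosing arrangements. Appendix 4 goes into detail on sectioning, antibodies, instruments and replicates, but does not say whether the person taking the measurement knows the cohort or the visit.

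This bears on a stated aim. The effect objective in Section 2 is about different dose levels, and dystrophin is the first effect parameter in the synopsis list. A reader who expects more signal at a higher dose, or at a particular visit, can shift semi-quantitative readings in that direction, and such a shift would look like a dose response. The readings also have a use beyond the report: the synopsis says that available effect data are taken into account when each boy's dose for treatment beyond the study period is decided.

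**Working it through.** No alpha, power, effect size or SD is stated for this read-out, so there is no figure of the plan to reproduce. The check has four parts.

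**1. Is masked reading stated anywhere?** Sections 5.2.1 (study period), 5.5.1 (beyond study period) and Appendix 4 were read for coded samples, a masked reader or an independent second reader. None is mentioned. Section 5.5.1 refers to a laboratory manual for collecting, processing and shipping the later biopsies, not for reading them. Section 5.2.1 refers to no manual.

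**2. Would ordinary labels hide the dose?** Dose level follows order of entry (Section 3.2.4). A subject number is given once the selection criteria are met (Section 5.1.2). If numbers run in that order, they reveal the cohort. The same laboratory handles the screening cells (Sections 5.1.2 and 5.1.4) and measures plasma PRO051 in the study period (Section 5.4), so it also holds exposure data.

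**3. How much within-subject anchoring is there?** Two biopsies per boy, counted from Section 5.2.1:

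| Patients | Cohort 1 size | All biopsies | Pre-treatment | Share | Boys with no pre-treatment study biopsy |
|---|---|---|---|---|---|
| 12 | 3 | 12 × 2 = 24 | 3 | 3/24 = 12.5% | 12 − 3 = 9 |
| 18, cohort 1 not expanded | 3 | 18 × 2 = 36 | 3 | 3/36 = 8.3% | 18 − 3 = 15 |
| 15, only cohort 1 expanded | 6 | 15 × 2 = 30 | 6 | 6/30 = 20% | 15 − 6 = 9 |

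Every pre-treatment study biopsy is in the 0.5 mg/kg cohort. Section 8.5.1 makes subjects their own reference, pre against post. For muscle dystrophin from study biopsies that is possible only in cohort 1. The other cohorts depend on day 43 against day 78 and on comparisons between cohorts.

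**4. Do triplicates help?** Write a reading as true level μ, plus a shift δ from knowing the cohort or visit, plus a boy effect (variance σ_b²), plus replicate error (variance σ_e²). For n boys read in triplicate:

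- expected cohort mean = μ + δ
- variance of the cohort mean = σ_b²/n + σ_e²/(3n)
- expected difference between cohorts A and B = (μ_A − μ_B) + (δ_A − δ_B)

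Replication divides σ_e² and leaves δ untouched. The documents give no value for δ. For illustration only, assume a common relative shift of 5% to 15% in all three boys of a cohort: the mean moves by (3 × 5%)/3 = 5% up to (3 × 15%)/3 = 15%. That restates the assumption and estimates nothing.

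**The case against.** The strongest reply is that the protocol is silent rather than wrong. Section 3.2.5 sits under Study treatments, where "Not applicable" is correct for an open single-arm study. A reader might infer that it declares masking of the assays irrelevant; it says nothing about them. Sample coding might also appear in a laboratory manual or in the cited method publication, neither of which is shown. That stands, and the point is limited to what the protocol itself fixes.

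The reading is also less free than it may look. Control proteins (laminin-alpha2, dysferlin), software intensity measurement and sequencing of the PCR products all constrain it. A reader might infer that protein load is varied from boy to boy at discretion. Appendix 4 more naturally describes a series of loads, 10 to 100 µg, run for each boy, although no rule says which load is reported.

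Nor do the effect conclusions rest on these readings alone. Timed tests, 6-minute walk, QMT and MMT are also effect parameters, exon skipping in blood cells has a visit 2 sample taken before the first dose, no primary endpoint is named, and dystrophin is reported descriptively. These facts lower the stakes. They do not protect the muscle comparison across doses, which none of those measures replaces.

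Finally, coding has limits. Primer sets depend on the boy's mutation, so RT-PCR cannot always hide the subject. Cohorts enter in sequence, so reading each boy's biopsies together still leaves cohort confounded with batch unless batches are linked. Both limits stand and shape the fix.

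**Conclusion.** The point holds as an inexpensive improvement to an exploratory read-out. The protocol does not mask the laboratory reader to cohort or visit, and order of entry can reveal dose level. With no control group and no pre-treatment study biopsy in cohorts 2 to 4, the descriptive comparison of dystrophin across doses and times is open to expectation bias that triplicates do not average out. The size of the bias is unknown. No formal test or sample size is affected.

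This rests on two assumptions: that no unseen manual already imposes coding, and that subject numbers follow order of entry.

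Three stronger statements are not supported. Nothing shows that bias has occurred or how large it would be. Coding would reduce reader bias, not abolish it. The laboratory is the sponsor's own only until 21 July 2011; after that it is the originator's. The missing baseline biopsies are a separate weakness that coding does not touch; Section 5.1.6 collects a past diagnostic biopsy result where one exists, but that is not a study biopsy.

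**What to change.** In Section 3.2.5 keep "Not applicable" for treatment and add a reference to Appendix 4 for assay reading. In Appendix 4, part II, state that:

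- sections, protein extracts and RNA carry random codes hiding cohort and visit, and the subject too where mutation-specific primers allow;
- a subject's biopsies are read together, in random slide and lane order;
- a common reference sample is run in every batch, so that cohorts read at different times can be compared;
- each subject's code is released once his values are locked.

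The same readers are used and no biopsy is added. The cost is a coding step, the reference sample and a short wait. In cohort 1 the pair is complete at day 43; in cohorts 2 to 4 the day 43 biopsy waits 78 − 43 = 35 days for its partner. The muscle PRO051 assay waits with it, because Section 5.2.1.3 places it after the mRNA and dystrophin results.

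Dose escalation uses safety data (Section 3.1) and is not delayed. The decision on each boy's dose beyond the study period does use effect data, so it would be wrong to say that no decision is affected. Locking per subject answers this: day 78 is 120 − 78 = 42 days before the last follow-up visit, which should leave time for his values to be available.
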